#### 2.9.2. Gut Microbiota Analysis

High-throughput sequencing will be used to detect gut microbiota information. Sequencing will be performed on the V4 region and the V3 to V4 amplification region of the 16S ribosomal RNA (rRNA) gene. The PE300 sequencing strategy will be used to carry out high-throughput sequencing on the Illunima Miseq platform (Illumina, San Diego, USA). The results will be analyzed using biological information after sequencing, and Pearson correlation analysis will be used to examine correlations between different indicators. QIIME software (http://qiime.org) will be used for operational taxonomic unit (OTU) clustering. The OTU representation sequence will be calculated using the Ribosomal Database Project Classifier based on the naïve Bayesian principle and compared with the reference sequences in the Silver database to obtain the species classification information corresponding to the OTU. The OTU cluster analysis results will be used to calculate the abundance index (Abundance-based Coverage estimator and Chao1 estimator), diversity index (Simpson and Shannon), and uniformity index to evaluate alpha diversity. Principal component analysis and principal coordinate analysis will be used to characterize beta diversity in the different groups.

#### 2.9.3. MRI Data Analysis

Brain parcellation will be performed using FreeSurfer (Dale, Fischl et al.1999; Fischl, Sereno et al. 1999; Fischl, Salat et al. 2002), and then, the parcellation and the functional connectivity will be combined to construct a functional brain network. FMRIB Software Library (FSL) developed by Oxford University (https://fsl.fmrib.ox.ac.uk/fsl/fslwiki/FSL) will be used to process high-resolution 3D T1-weighted anatomical images. The resting-state images will be preprocessed using the MATLAB toolkit SPM8 (http://www.fil.ion.ucl.ac.uk/spm/software/spm8) and resting-state fMRI (DPARSF) data processing kit (Resting-State fMRI Data Analysis Toolkit, REST, http://www.restfmri.net). Region-to-region functional connectivity will be computed between all the brain regions in CONN toolbox version 13 (http://www.nitrc.org/projects/conn). The connectivity correlation coefficients will then be used to construct the final functional network. Finally, the Graph Theoretic GLM tool (http://www.nitrc.org/projects/metalab_gtg) and in-house MATLAB workflow scripts will be used to calculate and analyze the functional brain network properties and organization from the subject-specific functional brain networks, and then, regional weighted network metrics indexing centrality will be computed.

#### 2.9.4. Tripartite Network Analysis

A tripartite network analysis based on graph theory will be used to compare the interactions among brain network activity, gut microbiota, and clinical data for migraineurs in the acupuncture and flunarizine groups. The interactions between the phenome (clinical symptoms), gut microbiome (fecal microbial community), and connectome (indices of regional centrality in the brain) will be analyzed using Spearman's correlations in MATLAB R2015b. Fisher's *r*-to-*z* transformation will be used to measure the correlation coefficient difference between the acupuncture and flunarizine group. The *Z* test will be applied, and an uncorrected value of *p* < 0.05 will be considered statistically significant. The software Cytoscape 3.7.2 (https://cytoscape.org) will be used to visualize and generate a brain activity, gut microbiota community, and clinical data interaction network. This association of this network will be included if Pearson's correlation for the data of the different groups achieves significance. The architecture of different group networks will be based on a significantly different network. The results will be described in terms of direct (correlations with microbial community) and indirect effects (clinical symptoms and brain connectivity metric) with an emphasis on the interaction between microbiome and clinical symptoms. An independent sample *t*-test will be used to examine between-group differences in clinical variables.

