#### 2.3.1. Inclusion Criteria

Eligible participants must meet the following criteria: (1) men or women aged 18–55 years; (2) right handed, length of education ≥6 years; (3) a history of migraine of, at least, 1 year with the first onset before the age of 50 years; (4) migraine attacks ≥2 times and number of migraine days <15 days per month during the past 3 months and baseline observation; (5) completion of the baseline headache diary; and (6) provision of written informed consent.

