### 2.4. Data Collection

At the 4-week baseline, patient demographic surveys (age, sex, height, weight, education, disease course, and medical history) will be administered. Clinical outcomes, fecal samples, and magnetic resonance imaging (MRI) data will be collected at the 4-week baseline, end of the 4-week intervention, and at the 12-week follow-up (Table 1).

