#### 2.4.3. MRI Data Acquisition

An MRI scan will be carried out using a 3.0TGE Signa MR750 system (GE Healthcare, Milwaukee, USA) in the Hospital of Chengdu University of TCM. High-resolution 3D T1-weighted anatomical images using a 3D spoiled gradient-recalled sequence will be produced. The acquisition parameters are as follows: repetition time (TR)/echo time (TE) = 5.97/1.96 ms, field of view (FOV) = 240 × 240 mm^2^, flip angle = 12°, matrix size = 512 × 512, 156 slices, and voxel size = 1 × 1 × 1 mm^3^.

Resting-state fMRI images will be obtained using a gradient-recalled echo planar imaging sequence with the following parameters: TR/TE = 2000/30 ms, FOV = 220 × 220 mm^2^, flip angle = 90°, matrix size = 64 × 64, 43 transverse slices without slice gap, voxel size = 3.75 × 3.75 × 3.2 mm^3^, and a total of 266 volumes for each subject.

MRI will be performed during the periovulatory phase (days 12–16 of the menstrual cycle) [47, 48]. All participants will be free from a typical migraine attack for, at least, 1 week prior to the MRI scan [47]. During the examination, subjects will be instructed to lie down with their eyes closed, not to think of anything, and particularly not to fall asleep. Foam padding will be used to restrict head motion, and earplugs will be used to attenuate scanner noise.

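### Section 2.9.4 builds its within-arm network edges from unadjusted pairwise correlations, so age or sex, which vary widely and are recorded at baseline, can create an edge without a brain-gut link

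*Protocol article*

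**What the plan says.** Section 2.9.4 (Tripartite Network Analysis) sets out three steps.

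- **Measure of association.** The interactions among clinical symptoms, the faecal microbial community and regional centrality "will be analyzed using Spearman's correlations in MATLAB R2015b".
- **Edge entry.** The rule names a different coefficient: "This association of this network will be included if Pearson's correlation for the data of the different groups achieves significance".
- **Comparison of arms.** Fisher's r-to-z "transformation will be used to measure the correlation coefficient difference between the acupuncture and flunarizine group", followed by a Z test at an uncorrected threshold of 0.05.

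No covariate, partial correlation or stratification is named at any of these steps. On interpretation the section says: "The results will be described in terms of direct (correlations with microbial community) and indirect effects (clinical symptoms and brain connectivity metric").

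The patient characteristics are described elsewhere. Section 2.3.1 admits "men or women aged 18–55 years". Neither 2.3.1 nor 2.3.2 limits weight or BMI. Under section 2.4, at baseline, "patient demographic surveys (age, sex, height, weight, education, disease course, and medical history) will be administered".

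**The concern.** An edge is a correlation between two layers across the patients of one arm. Suppose that age or sex is related both to a centrality index and to a taxon. The two will then be correlated even if neither influences the other. Randomisation makes the arms comparable with each other, but it does not remove a common cause of two variables within an arm.

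The third objective in section 2.1 concerns correlations among symptom improvement, brain change and microbiota regulation brought about by the treatments, and section 2.9.4 will describe the edges as effects. An edge that arises from age or sex could then be reported as part of a brain-gut mechanism, although the data needed to check this are already collected.

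**Working it through.** **1. Number of patients behind each correlation.** Section 2.5.1 assumes changes of 4.1 (SD 3.5) and 1.9 (SD 2.3), α = 0.05 and power 0.80. The common SD is √((3.5² + 2.3²)/2) = 2.961, so d = 2.2/2.961 = 0.743. A two-sided two-sample t-test (noncentral t) needs 30 per group, with power 0.808. This reproduces the stated 30. The total of 66 is 2 × 33, with 33 = 30 × 1.1. The main calculation below uses n = 30 per arm.

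**2. Correlation induced by a shared trait.** Let trait T correlate a with X and a with Y, and let X and Y be independent given T. Then corr(X, Y) = a × a. The documents give no value of a, so the range is an assumption: a = 0.2, 0.3, 0.4, 0.5 gives 0.04, 0.09, 0.16, 0.25.

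**3. Chance that the false edge is significant: approximation.** On the Fisher-z scale the SE is 1/√(n − 3), and the rejection probability is P(Z > 1.96 − m) + P(Z < −1.96 − m), with m = atanh(a²) × √(n − 3). At n = 30, √27 = 5.196:

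| a | a² | m | probability |
|---|---|---|---|
| 0.2 | 0.04 | 0.208 | 5.5% |
| 0.3 | 0.09 | 0.469 | 7.6% |
| 0.4 | 0.16 | 0.839 | 13.4% |
| 0.5 | 0.25 | 1.327 | 26.4% |

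With all 33 enrolled patients per arm, a = 0.3, 0.4 and 0.5 give 7.8%, 14.3% and 28.8%.

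**4. The same by simulation, with the named coefficients.** There were 20,000 replicates of normal data at n = 30. The partial Spearman adjusts for T. The last column is the Fisher-z test between two arms that share the same a.

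| a | Spearman | Pearson | Partial Spearman | Difference between arms |
|---|---|---|---|---|
| 0.2 | 5.4% | 5.4% | 5.1% | 5.0% |
| 0.3 | 7.2% | 7.6% | 5.2% | 5.0% |
| 0.4 | 12.5% | 13.4% | 5.1% | 5.1% |
| 0.5 | 24.4% | 27.1% | 5.1% | 5.2% |

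Within-arm edges are inflated once a exceeds about 0.3. Adjustment restores the nominal rate, and the comparison between arms stays at its nominal level throughout.

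**5. Levels or changes.** If X before = aT + e₀ and X after = aT + e₁, then the change is e₁ − e₀ and T drops out. A stable trait confounds a correlation of changes only if it predicts the change on both layers. Section 2.9.4 does not say whether levels or changes are correlated.

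**6. Price of adjustment.** With k covariates the Fisher-z SE is 1/√(n − 3 − k). At n = 30:

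- no covariate: 1/√27 = 0.192
- two covariates: 1/√25 = 0.200 (√(27/25) = 1.039, 4% wider)
- three covariates: 1/√24 = 0.204 (√(27/24) = 1.061, 6% wider)

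**The case against.** **The article is silent on covariates, and an analysis plan may add them.** This is fair as far as it goes: the text does not rule adjustment out, and a reader should not infer that the trial will certainly leave these traits unadjusted. But section 2.9.4 is specific down to software version, transformation, threshold and edge rule. The method it names is an unadjusted correlation, and that stated method is what is assessed here.

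**The inferential step is the comparison of arms, and it is sound.** This stands. A reader might infer that confounding by age or sex also invalidates the between-arm test. The documents do not support that: allocation is random, the same dependence is expected in both arms, and the simulated error rate stays near 5%. The point is confined to the edges within each arm and how they are read.

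**The size is assumed.** This also stands. Nothing in the documents gives the correlation of age or sex with centrality, taxa or symptoms. At 0.2 the effect is negligible and at 0.3 it is small. It would be wrong to conclude that most drawn edges will be spurious.

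**The third objective is about change, where stable traits largely cancel.** This is correct and weakens the point, but section 2.9.4 does not commit to change scores.

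**The design already controls much.** Diet before stool sampling, recent antibiotics, digestive disease and recent attacks are restricted, and "MRI will be performed during the periovulatory phase (days 12–16 of the menstrual cycle"). These help, but they do not narrow age or remove the difference between the sexes. A reader might take the cycle-phase rule as a defect because men have no equivalent; it is not one.

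**Adjustment is not automatically right for BMI.** This is accepted. Body mass may share a pathway with the microbiota, so adjusting for it could remove real signal. It belongs in a sensitivity analysis.

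**Conclusion.** The point holds as a worthwhile, inexpensive improvement to a stated method. It is not an error that undermines the trial. Unadjusted within-arm edges can reflect a measured common cause, and the plan's description of them as direct and indirect effects claims more than such correlations can show.

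The false-edge rates of about 5%, 7%, 12% and 24% rest on four assumptions: one trait with equal correlation (0.2 to 0.5) to both layers, no other link between the layers, normally distributed data, and 30 patients per arm. They describe correlations of levels, or of changes if the trait predicts response on both layers. Otherwise the inflation is smaller. The between-arm Fisher-z comparison is unaffected when the trait acts equally in both arms.

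**What to change.** In section 2.9.4:

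1. Replace the plain correlations by partial Spearman correlations adjusted for baseline age and sex, with the degrees of freedom reduced accordingly.
2. Use this one measure for edge entry, which also resolves the mismatch between Spearman and Pearson. Use it in the between-arm comparison as well, for consistency and not because that test needs repair.
3. Add BMI, computed from the recorded height and weight, as a sensitivity analysis.
4. Show the unadjusted network alongside the adjusted one.
5. Describe edges as associations, not as direct or indirect effects.

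The cost is a few sentences and a different function call, with no new data. The statistical price is two degrees of freedom per arm, or three with BMI, which widens Fisher-z intervals by about 4% or 6% at n = 30. If few men enrol, the sex adjustment will rest on a handful of patients and be imprecise, so the number of men per arm should be reported with the network. Adjustment deals only with the traits that are entered; unmeasured common causes remain, which is a further reason for the wording in item 5.

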## 2. Methods and Design

### 2.1. Objectives

This study aims to (1) re-evaluate the efficacy of acupuncture and flunarizine on migraine treatment; (2) compare the similarities and differences in brain activity and gut microbiota associated with acupuncture and flunarizine treatment for migraine; and (3) investigate the correlation between symptom improvement, brain activity changes, and gut microbiota regulation elicited by acupuncture and flunarizine.

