#### 2.4.1. Clinical Data Collection

All participants will be instructed to complete a headache diary every 4 weeks during the study. The headache diary will mainly record the time of migraine onset, migraine duration, migraine severity (detected by a visual analog scale), and use of rescue medicine.

The following clinical outcomes will be assessed by independent assessors who have been trained before participating in the study. The primary outcome is the change in frequency of migraine attacks, and the secondary outcomes include the changes in migraine days (days on which migraine attacks occurred), average migraine severity, gastrointestinal symptoms, psychiatric symptoms, and quality of life. The intensity and frequency of gastrointestinal symptoms will be assessed using the Gastrointestinal Symptom Rating Scale (GSRS) [42, 43]. As migraine is often accompanied by psychiatric symptoms, the Beck Anxiety Inventory (BAI) [44] and the Beck Depression Inventory (BDI) [45] will be used to measure the emotional states of migraineurs, and quality of life will be assessed using the Migraine-Specific Quality of Life Questionnaire (MSQ) [46].

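### The tripartite network analysis tests between-arm differences in correlation at an uncorrected p < 0.05, so some network difference is near-certain even if none exists

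*Protocol article*

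**What the plan says.** Section 2.9.4 correlates three blocks of variables by Spearman's method: clinical symptoms, the fecal microbial community and regional brain centrality. Of Fisher's r-to-z it says: "transformation will be used to measure the correlation coefficient difference between the acupuncture and flunarizine group". A Z test follows, and the threshold is explicit: "an uncorrected value of *p* < 0.05 will be considered statistically significant".

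The use made of the result is also stated: "The architecture of different group networks will be based on a significantly different network". One further screen appears there. An association enters the network if a Pearson correlation reaches significance, with no correction mentioned.

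The blocks are described without counts. Section 2.9.3 says "Region-to-region functional connectivity will be computed between all the brain regions in CONN toolbox version 13", and Section 2.9.2 says "QIIME software (http://qiime.org) will be used for operational taxonomic unit (OTU) clustering". Section 2.4.1 gives about seven clinical measures: attack frequency, migraine days, severity, GSRS, BAI, BDI and MSQ.

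The analysis serves objective 3 in Section 2.1: "investigate the correlation between symptom improvement, brain activity changes, and gut microbiota regulation elicited by acupuncture and flunarizine". No section adds familywise or false discovery control, a global test of the network, or a limit on taxa or regions.

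**The concern.** The plan does not leave multiplicity open for a later document. It fixes the threshold and says that it is uncorrected. Each cross-domain pair gets its own 5% test, the passing pairs are called statistically significant, and the reported network rests on them. With many pairs, chance alone supplies passing pairs.

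At stake is whether the network comparison can tell two situations apart: acupuncture and flunarizine acting through different brain-gut relations, or through the same ones. If a difference appears almost always, its appearance says little.

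**Working it through.** **The plan's own figure.** No error rate is stated for this analysis. The only computed figure is the sample size in Section 2.5.1, which supplies n here. With changes of 4.1 (SD 3.5) and 1.9 (SD 2.3), d = 2.2 / sqrt((3.5² + 2.3²)/2) = 0.743. A two-sided t-test has power 0.794 at 29 per arm and 0.808 at 30, so 30 per arm reproduces. With the allowance for withdrawals it is 33.

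**Number of pairs (assumed).** With S clinical variables, T taxa and R regions, the cross-domain pairs are m = S·T + S·R + T·R. S = 7 follows Section 2.4.1; T and R are assumptions.

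- R = 5, T = 3: 21 + 35 + 15 = 71
- R = 10, T = 10: 70 + 70 + 100 = 240
- R = 68, T = 30: 210 + 476 + 2,040 = 2,726
- R = 100, T = 50: 350 + 700 + 5,000 = 6,050

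**Expected false edges with no true difference.** 0.05 × m gives 3.6, 12, 136 and 303. For independent tests the chance of at least one is 1 − 0.95^m. This is already 0.95 at m = 59 and 0.994 at m = 100.

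**Null simulation.** The real tests are not independent, so the procedure was simulated: Spearman correlations, Fisher z difference, two-sided Z test at 0.05. It used 30 and 33 patients per arm and 300 replicates per setting, with several correlation structures, each the same in both arms. The Pearson rule was taken as p < 0.05 in at least one arm.

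| Pairs | Mean false edges, Z test | Chance of ≥ 1 | Mean after Pearson rule | Chance of ≥ 1 |
|---|---|---|---|---|
| 71 | 3.4–4.0 | 0.88–0.98 | 1.9–3.4 | 0.74–0.91 |
| 240 | 11.5–13.1 | 0.99–1.00 | 6.8–10.9 | 0.97–1.00 |
| 2,726 | 130–142 | 1.00 | 75–118 | 1.00 |
| 6,050 | 305–322 | 1.00 | 179–263 | 1.00 |

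The Z test passes about 5% of pairs. The Pearson rule lowers this to about 3 to 4.5%.

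**What 30 per arm can detect.** The standard error of a Fisher z difference is sqrt(2/27) = 0.272. Uncorrected significance needs 1.96 × 0.272 = 0.53, for example r = 0 against 0.49. With 2,726 pairs, the first Benjamini–Hochberg step is 0.05/2,726 = 1.8 × 10⁻⁵, a normal quantile of 4.28. That needs 4.28 × 0.272 = 1.17, or r = 0 against about 0.82.

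**The case against.** **The number of pairs is not documented.** A reader might infer thousands of tests from a whole-brain parcellation crossed with OTU data. That is plausible, but the article gives no number of regions, taxonomic level or selection step, so the larger counts remain assumptions. The conclusion does not need them, since 240 pairs suffice.

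**The Pearson rule also screens edges.** It does, so 5% of pairs overstates the drawn network. Read as significance in at least one arm, it leaves most false edges in place. The wording does not exclude a stricter reading, significance in both arms. With zero true correlation, a pair would then pass almost only with opposite signs, at a rate near 0.05 × 0.05 / 2 = 0.00125: about 3.4 edges at 2,726 pairs and 0.3 at 240. On that reading the drawn network would be much smaller, and at 240 pairs usually empty. The Z tests declared significant would still run at 5%.

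**The work is exploratory.** The Introduction does speak of exploring relationships, and the Discussion hopes only for partial answers. But Section 2.9.4 does not label the analysis exploratory, and it calls its results statistically significant. The missing correction is disclosed, which lets a careful reader discount single edges, but it does not supply a valid test.

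**The role should not be inflated.** One might call this the trial's main mechanistic claim. The documents do not rank it so: objective 3 concerns correlations among changes and does not itself state a between-arm difference, while objective 2 also rests on the analyses in Sections 2.9.2 and 2.9.3.

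**Conclusion.** The point holds. The stated rule has no control over false edges, and a between-arm network difference is near-certain when none exists: about 12 false edges at 240 pairs (7 to 11 after the Pearson rule) and about 136 at 2,726 pairs (75 to 118 after it). These figures assume seven clinical variables, the stated block sizes, about 30 patients per arm and the at-least-one-arm reading of the Pearson rule.

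A reader might go further and say that the analysis cannot fail to show a difference. That is too strong: with 71 pairs the chance after the Pearson rule is 0.74 to 0.91, and the both-arms reading would lower it. Nor does the flaw reach the primary outcome, the sample size or the clinical analysis in Section 2.9.1. It should be fixed, but it does not threaten the trial's primary result.

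**What to change.** In Section 2.9.4, replace the uncorrected rule as follows.

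1. Make the between-arm inference one global permutation test: permute arm labels and use the number, or the sum, of differing edges as the statistic.
2. Call an individual edge statistically significant only if it survives Benjamini–Hochberg at q < 0.05 over all cross-domain pairs tested. Permutation p-values are preferable. In the simulation, Bonferroni limits using the Fisher z approximation gave familywise error of about 0.04 to 0.11 rather than 0.05, so the approximation is somewhat liberal in the far tail at this sample size.
3. Show edges at uncorrected p < 0.05, if at all, as hypothesis-generating.
4. State the number of regions and taxa, and whether the Pearson rule applies to one arm or both. Edges are computed by Spearman but admitted by Pearson; use one coefficient.

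The cost is a little more analysis work and no new data. The real price is in results: at 30 per arm few or no single edges may survive, since with 2,726 pairs a lone edge must show roughly r = 0 against 0.82. The global test would then carry the between-arm conclusion. Fixing a smaller set of taxa and regions in advance would ease this.

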### 2.5. Sample Size, Randomization, and Blinding

#### 2.5.1. Sample Size Calculation

Following a previous study, we anticipate that the change in the average number of migraine days in the acupuncture group will be 4.1 ± 3.5, and in the flunarizine group, it will be 1.9 ± 2.3 [37]. Assuming that *α* = 0.05 and 1 − *β* = 0.80, 30 patients will be required for each group, as calculated using *G*^*∗*^Power V3.1.9.2 software. There is no consensus on sample size for neuroimaging and gut microbiota research. A review of previous similar studies suggests that 12–27 individuals in each group is a reasonable sample size for stable and reliable results [49, 50]. Finally, a total of 66 patients will be recruited to compensate for a withdrawal rate of 10%.

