### 2.9. Statistical Analysis

#### 2.9.1. Clinical Data Analysis

The analysis plan will be determined before the study is conducted. Demographic characteristics, baseline characteristics, and clinical outcomes will be analyzed using SPSS25.0 statistical software based on the intention-to-treat population, which comprises subjects who receive, at least, one treatment and undergo, at least, one posttreatment efficacy evaluation. Missing data will be replaced by data from the last observation. Normally distributed continuous variables will be presented by means and standard deviations with 95% confidence intervals. Nonnormally distributed continuous variables will be described using medians and interquartile ranges. Categorical variables will be described using percentages and frequencies. The significance level used for statistical analysis with 2-tailed testing will be 5%. Qualitative data will be compared using the chi-square test. If the quantitative data are normally distributed, we will use analysis of variance to detect differences between the two groups; if not, the Mann–Whitney test will be used. Data sheets will be anonymized for data entry, and statistical analysis will be conducted by an independent statistician blinded to treatment allocation.

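### Section 2.9.4 selects network edges on Pearson's correlation but analyses them and compares the arms on Spearman's; one coefficient should serve throughout

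*Protocol article*

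**What the plan says.** Three statements in section 2.9.4 (Tripartite Network Analysis) bear on the same associations.

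- **Estimation.** The interactions among clinical symptoms, the faecal microbial community and regional brain centrality "will be analyzed using Spearman's correlations in MATLAB R2015b".
- **Arm comparison.** Fisher's r-to-z "transformation will be used to measure the correlation coefficient difference between the acupuncture and flunarizine group". A Z test follows, and an uncorrected p below 0.05 "will be considered statistically significant". Spearman is the only coefficient named before this test, so the natural reading is that Spearman coefficients are transformed.
- **Edge inclusion.** "This association of this network will be included if Pearson's correlation for the data of the different groups achieves significance".

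The section does not say that two coefficients are intended, why, or which prevails. Section 2.9.2 (Gut Microbiota Analysis) states separately that "Pearson correlation analysis will be used to examine correlations between different indicators". That sentence does not reconcile the statements in 2.9.4.

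**The concern.** Spearman measures monotone association through ranks; Pearson measures linear association on the scale on which the data enter. They estimate different quantities and can lead to different decisions in the same sample. Under the text as written, an association may differ significantly between arms on Spearman and never appear in the network, because Pearson was not significant. The converse can also occur: an edge is drawn on Pearson with no Spearman association behind it.

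Objective 3 in section 2.1 concerns the correlation between symptom improvement, brain activity and gut microbiota, and the tripartite network is the tool for it. Section 2.9.4 also bases the architecture of the group networks on what differs significantly, so the inclusion rule and the arm test together determine the reported picture. If the coefficient is settled only after the data are seen, it can be chosen by which network looks better.

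**Working it through.** **1. Number of patients per correlation.** Section 2.5.1 states that "30 patients will be required for each group", from changes in migraine days of 4.1 (SD 3.5) and 1.9 (SD 2.3), α = 0.05 and power 0.80.

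- Pooled SD = √((3.5² + 2.3²)/2) = √8.77 = 2.961.
- Standardised difference = (4.1 − 1.9)/2.961 = 0.743.
- Two-sided noncentral t: power 0.794 at 29 per group and 0.808 at 30. The stated 30 reproduces.

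The network section gives no sample size of its own, so n = 30 per arm is used. Recruitment is 66, or 33 per arm, and n = 33 was run as well.

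**2. Set-up (assumptions, not in the documents).**

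- Latent pair (a, b) is bivariate normal with correlation ρ. The taxon is x = a (normal) or x = exp(s·a) (log-normal, log-SD s = 1, 1.5 or 2); the partner variable is b.
- Each coefficient is tested within one arm at two-sided 5%: significant if |r| > t/√(n − 2 + t²), with t the 97.5% point on n − 2 degrees of freedom. At n = 30, t = 2.048 and the threshold is 2.048/√(28 + 4.19) = 0.361.
- Disagreement is the share of samples in which exactly one of the two tests is significant. There were 20,000 samples per setting, so the Monte Carlo standard error of a proportion is at most √(0.25/20,000) ≈ 0.0035.

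**3. Results at n = 30, ρ = 0.5.**

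| Taxon | Pearson power | Spearman power | Disagreement |
|---|---|---|---|
| Normal | 0.83 | 0.78 | 9% |
| Log-normal, s = 1 | 0.68 | 0.77 | 21% |
| Log-normal, s = 1.5 | 0.55 | 0.77 | 32% |
| Log-normal, s = 2 | 0.46 | 0.77 | 41% |
| s = 1.5 with 40% zeros | 0.57 | 0.72 | 29% |

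A second run gave Pearson 0.68, 0.56 and 0.46 for the three log-normal rows, and 0.82 against 0.77 for normal data. The differences are of the order of simulation error.

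**4. Other settings.**

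- At ρ = 0.3, disagreement is 12% for normal data and 21%, 26% and 28% for s = 1, 1.5 and 2.
- At n = 33 and ρ = 0.5 it is 8% for normal data and 19%, 31% and 40% for s = 1, 1.5 and 2.
- With no association, each test holds about 5%. At s = 1.5, however, only 18% of the false edges flagged by either test are flagged by both.
- If the outcome is instead linear in raw abundance (s = 1, correlation 0.5), Pearson has power 0.65 and Spearman 0.41, with 30% disagreement.

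**5. What this does and does not measure.** The runs compare the two inclusion decisions within one arm. They do not simulate the two-arm Z test, so they show how often the coefficients part company, not how often a significant arm difference would be lost.

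**The case against.** The strongest reply is that the text can be carried out as written. One sentence governs what is drawn in Cytoscape and another governs the arm comparison, so a Pearson filter beside a Spearman comparison is odd but not impossible. It may be no more than a naming slip. The network is also remote from the trial's main conclusions. This much stands: inconsistent is the right word rather than unworkable, and the consequence is confined to the mechanistic aim. It does not remove the mismatch, because the sentences name different statistics for the same edges and no rule links them. Nor is it detail that a condensed article leaves to its analysis plan, since the article itself states both.

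A reader might infer three stronger points, which the documents do not support.

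- *Pearson loses power on microbial data.* This holds if skewed abundances enter untransformed and the association lies on the log scale. The article states neither. With normal data, or an association linear in raw abundance, Pearson is the more powerful.
- *The arm comparison has an inflated error rate because Fisher's Z is applied to Pearson coefficients from skewed data.* On the natural reading the plan transforms Spearman coefficients, so such a figure would describe a test that is not planned.
- *Section 2.9.2 must also abandon Pearson.* That sentence speaks of indicators, not taxa, and the section's indices include per-sample richness and diversity summaries. Pearson there contradicts nothing in 2.9.4.

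**Conclusion.** The inconsistency is real and should be corrected. It follows from the text alone and holds for any distribution of the data. Its size depends on assumptions: at 30 per arm and a latent correlation of 0.5, the two tests give different inclusion decisions in about 9% of samples for normal data and 21% to 41% for log-normal taxa with log-SD between 1 and 2. The power consequence is conditional and can run either way: about 9 to 31 percentage points against Pearson in the log-scale settings (0.77 − 0.68 = 0.09; 0.77 − 0.46 = 0.31), and 24 points in its favour in the raw-scale setting (0.65 − 0.41 = 0.24). The primary outcome, the clinical analysis in 2.9.1 and the sample size are unaffected.

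**What to change.** Use one coefficient in section 2.9.4 for edge estimation, edge inclusion and the between-arm test. Spearman is the natural choice, because the section already names it for the analysis: in the inclusion sentence, put Spearman's in place of Pearson's. Settle this before the network data are analysed.

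Referring the arm difference to a permutation distribution, or using a variance derived for Spearman coefficients in the Z test, is an optional refinement. No change to 2.9.2 is required.

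The cost is one word in the text and at most a line of analysis code, with no effect on recruitment, data collection or the clinical analyses.
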